### Patient Population—Inclusion and Exclusion Criteria

The study will include patients entered in the Alabama stroke system by EMS with suspected LVO based on an EMSA ≥ 4 with one point scored for each abnormal response on the 6-item scale. The study will exclude patients with stroke onset while hospitalized, a time last known well ≥24 h prior to initial EMS contact, and patients who only respond to pain or who are unresponsive based on the Alert, responds to Voice, responds to Pain and Unresponsive Scale (19). The flow of patients during the study is shown in Figure 3.

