### Intervention

The implementation of TCC Coordinated SBST will be carried out under the auspices of the ADPH with the overarching goal to address current stroke system challenges. The *sine qua non* of this initiative is coordination of SBST by the TCC. Because this is a statewide initiative and the TCC serves the entire state, some elements of the intervention such as the use of the EMSA will be standardized across the state, as shown in Table 1. At the level of EMS regions and stroke centers, however, the specific strategies used to achieve TCC Coordinated SBST will be tailored to the specific context. Context-specific adaptation will depend on local resources and practice. For example, longer travel times in rural compared to urban regions might prompt longer additional transport time limits in rural regions to route a patient past a non-MTC to a MTC. Another example is that non-MTCs will have variable imaging and telestroke capability and hence site-specific code stroke protocols. Acute stroke system challenges, TCC Coordinated SBST core functions, and context-specific forms that might be used to achieve the core functions are shown in Table 2. Implementation plans are as follows:

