(1) EMS Training in the EMSA: As previously noted, our model was designed to address barriers to prehospital stroke care (16, 17), by focusing training, experience, and feedback on the TCC paramedic communicators. However, we applied what we have learned from our preliminary study to enhance our training program for EMS providers in the field (15). For example, we included explicit strategies in the EMSA to enable determination of abnormal horizontal gaze or lateralized weakness of the face, arm, or leg in confused or aphasic patients. The training program was also informed by prior qualitative studies on paramedic decision-making for high acuity patients (mostly trauma) that have found a reliance on the paramedic's initial “gut” impression (33) and a study that found that the diversity of stroke presentations was a barrier to acute stroke recognition by paramedics (34). We addressed these issues by providing “snapshot” figures representing left and right middle cerebral artery syndromes in addition to training on individual scale items to aid EMS providers who favor a gestalt approach to diagnosis. We created two training videos for presentation at regional zoom kick-off events including EMS agencies and hospitals. A 24 min video, “Severity-Based Stroke Triage: Key Concepts,” covers the State's plan for roll-out of severity-based stroke triage, stroke vs. stroke mimics, large vessel occlusion, the EMSA, treatment options for acute ischemic stroke, and the concept of time last known well (35). The other video is a 9 min demonstration of the “Emergency Medical Stroke Assessment” by paramedics (36). After the regional kick-off events, paramedics across the state were required to view the training videos and complete a 20 question post-training examination. The EMS training videos and examination take <90 min to complete.(2) EMS stroke severity assessment and prenotification: After statewide EMSA training is complete, TCC Guided EMSA with item-specific prenotification and focused feedback will be expanded to all EMS regions in Alabama. Key elements from the preliminary study that have been incorporated into the current protocol include TCC guidance of EMS performance of the EMSA when needed, item-specific prenotification by TCC rather than a summary score, and ongoing review of recorded interactions between TCC and EMS with feedback to TCC to enhance their guidance skills (15). During the standard triage data collection period in each EMS region, all stroke patients (including those with suspected LVO based on an EMSA ≥ 4) will undergo triage to the nearest stroke center with capacity of any level (Figure 3). Additional training for TCC will be employed as needed to optimize performance of the TCC Guided EMSA.(3) Prehospital Severity-Based Stroke Triage: Plans will be developed during the standard triage period in each region considering EMS and hospital resources, levels and numbers of stroke centers, travel times by ground and air in each region, and data from focus groups and interviews. A schematic of the flow of patients within each EMS region during SBST implementation is shown in Figure 3. During implementation, patients entered into the stroke system by EMS who have an EMSA ≥ 4 with a time last known well ≤ 24 h who are alert or respond to voice will be triaged as follows: If direct transport to a MTC (including comprehensive stroke centers and thrombectomy-capable primary stroke centers) complies with region-specific transport time limits and will not preclude use of tPA, TCC will coordinate pre-notification and air or ground transport to a MTC. If direct transport time to a MTC is greater than region-specific limits or transport to a MTC will preclude use of tPA, TCC will coordinate pre-notification and air or ground transport to the closest available stroke center of any level and initiate a region and hospital specific plan to expedite inter-facility transfer to a MTC.(4) Emergency Department Severity-Based Stroke Triage: The implementation strategy includes an educational conference to be held in each region to review regional implementation plans, foster engagement of stroke center personnel and EMS, provide a “toolkit” of resources to streamline care, and train stroke coordinators throughout Alabama. The grant supports reimbursement for stroke coordinators who successfully pass the Stroke Certified Registered Nurse examination offered American Board of Neuroscience Nursing (37). The plan includes interviews and focus groups with stroke center directors and coordinators, on-site evaluation if possible, protocol development, and training on stroke treatment options and the EMSA. We will encourage EMSA performance systematically as part of code strokes on patient arrival. Depending on available resources, context specific forms might include multimodal computerized tomography (CT) including noncontrast CT, CT angiography, and CT perfusion on code stroke patients with suspected LVO, telestroke or image sharing with MTCs, and transitioning from alteplase to tenecteplase to facilitate rapid treatment and transfer.(5) Inter-facility Severity-Based Stroke Triage: Plans for secondary triage will be developed during the standard triage period and will depend on regional resources as well as data from focus groups and interviews. The plan includes TCC monitoring of the status of patients with suspected LVO who are initially transported to non-MTCs, modeled after the TCC Trauma system process. In this process, the TCC follows up with the ED every 20 min to update patient status and identify the best options for secondary triage in real-time. Context specific strategies might include holding the EMS unit involved with primary triage of patients with suspected LVO at the non-MTC until a transfer decision is made or tPA is initiated, modeled after the Alabama Trauma system “Rescue Stop.” Alternatively, TCC might proactively mobilize ground or air resources to achieve rapid patient transfer.

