**Prehospital SBST** • Limited adoption of SBST • Limited data to support SBST	• Interviews with EMS Regional Directors to develop region/county specific SBST transport protocols • TCC assists in choice of destination and coordination of transport mode (ground vs. air)	• Longer transport limits in rural and suburban regions compared to urban locations • Modification of transport limits by resource availability • Air transport from rural locations when weather permits • Patient “hand-off” from one EMS unit to another to facilitate longer transports and keep units available in regions with limited EMS resources • Mobilization of back-up EMS units in regions with limited EMS resources when an out of region transport is initiated
**Emergency Department (ED) SBST** • Variable LVO scale use in the ED • Delays to cerebrovascular imaging • Delays to initiation of transfer process at non-MTCs • Delayed mobilization of team for inter-facility transfer • Limited transport resources, especially in rural areas	• Interviews with stroke center directors and coordinators to develop stroke center protocols • Regional symposia to review SBST plans, train coordinators, and provide “toolkit” to streamline ED stroke care • Active TCC monitoring in the ED every 20 min for suspected LVO patients prior to transfer • TCC assists in choice of MTC for transfer	• EMSA or another LVO scale included in code stroke on patient arrival • NIHSS included in code stroke on patient arrival • Combined CT/CTA on code stroke patients with suspected LVO • Combined CT/CTA/CTP on code stroke patients with suspected LVO • Telestroke consultation • Image sharing with MTC • Transition from alteplase to tenecteplase to facilitate rapid treatment and transfer • TCC proactively mobilizes transport team for secondary triage • Initial EMS unit remains until transfer decision is made (“Stroke Rescue Stop”) • Mobilization of neuro-interventional team once transfer decision is made • Transport to MTC ED or directly to angiography suite

*TCC, Trauma Communications Center; SBST, Severity-Based Stroke Triage; LVO, Large Vessel Occlusion; MTC, Mechanical Thrombectomy Center; CT, Computerized Tomography; CTA, CT Angiography; CTP, CT Perfusion*.

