### Secondary Outcomes

Consistent with the aims of implementation research, in addition to effectiveness, we seek to fully assess change in the broad public health impact before and after implementation of TCC Coordinated SBST using the RE-AIM (Reach, Effectiveness, Adoption, Implementation, and Maintenance) framework (AIM 2) (38, 39). The public health outcomes of TCC Coordinated SBST across RE-AIM dimensions are shown in Table 3. There may be unintended negative consequences to implementation of TCC Coordinated SBST, including delay in access to tPA and longer EMS response times. We address these concerns by explicitly tracking the impact of the intervention on these outcomes (see Table 3). Another concern is overloading MTCs with patients without LVO due to false positive screens and reducing capacity of MTCs to accept transfers of patients for MT. In part, we are hoping to mitigate against this by adding a designation in Alabama for thrombectomy-capable primary stroke centers. We will also track the proportion of LVO patients requiring inter-facility transfer, the timeliness of transfer, and rate of MT among all confirmed LVO strokes for patients entered into the Alabama Stroke System (see Table 3). As part of the stepped wedge trial, we will collect data on the rate of true positive and false positive LVO screens. Because statewide stroke system data collection will include whether an LVO was confirmed, LVO location, and whether the patient received MT, we will be able to determine the rate of true negative and false negative LVO screens, and accordingly, sensitivity and specificity of prehospital LVO screening.

**Table 3 T3:** RE-AIM framework to evaluate the public health impact of TCC Coordinated SBST.

**RE-AIM dimension**	**Outcomes**	**Data source**
**Reach**	• Proportion of Alabama MT patients who undergo TCC Coordinated SBST	• ADPH RESCUE ePCR and LifeTrac database
	• Differential reach by race, ethnicity, sex, and population density	• ADPH RESCUE ePCR and LifeTrac database
**Effectiveness**	• Proportion and timeliness of MT for EMS-suspected LVO	• LifeTrac and ADPH REDCap databases
	• Proportion and timeliness of MT for all confirmed Stroke System LVO	• LifeTrac and ADPH REDCap databases
	• Proportion and timeliness of tPA treatment	• LifeTrac and ADPH REDCap databases
	• Proportion requiring inter-facility transfer and timeliness of transfer	• LifeTrac and ADPH REDCap databases

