### Data Management of Embedded Stepped Wedge Cluster Trial

Data sources are shown in Figure 4 and will include the following: (1) Expanded LifeTrac data entry by TCC on all stroke system patients to include prehospital EMSA items (collected in real-time by TCC communicators), abstracted hospital data collected by stroke coordinators including whether an LVO was confirmed, LVO location, and whether the patient received MT and embedded LifeTrac data collection by TCC on patients with EMS-suspected LVO who meet study entry criteria to both guide and document the prehospital triage process in real-time; (2) Study patient ED and hospital data entered by stroke coordinators into an ADPH REDCap database, and (3) System level data captured by ADPH's Recording of Emergency Medical Services Calls and Urgent-care Environment electronic Patient Care Reports to allow determination of the proportion of Alabama MT patients who undergo TCC Coordinated SBST, county and regional EMS response times, proportion of EMS organizations and stroke centers participating, and data on fidelity and maintenance of implementation. REDCap is a secure, HIPAA-compliant, web-based application for supporting data capture for research studies (41). The ADPH REDCap database was developed specifically for this study and will include applicable NINDS Common Data Elements from ED and hospital medical records including the National Institute of Health Stroke Scale (42, 43) and a structured telephone modified Rankin Scale (44, 45) at 3 months post-stroke.

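### Sensitivity and specificity of the prehospital LVO screen cannot be determined as claimed, because nothing requires vessel imaging in screen-negative patients

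*Protocol article*

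**What the plan says.** A positive screen is "suspected LVO based on an EMSA ≥ 4 with one point scored for each abnormal response on the 6-item scale" (Patient Population). The screen is recorded on both sides of that cut-off: Data Management describes "Expanded LifeTrac data entry by TCC on all stroke system patients to include prehospital EMSA items".

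The reference standard is the hospital record. LifeTrac is to hold "abstracted hospital data collected by stroke coordinators including whether an LVO was confirmed, LVO location, and whether the patient received MT". From this the Secondary Outcomes section draws its conclusion: "Because statewide stroke system data collection will include whether an LVO was confirmed, LVO location, and whether the patient received MT", the article says, "we will be able to determine the rate of true negative and false negative LVO screens, and accordingly, sensitivity and specificity" of the prehospital screen follow.

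On who receives vessel imaging:

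- Intervention, opening paragraph: "non-MTCs will have variable imaging and telestroke capability and hence site-specific code stroke protocols".
- Intervention, item 4 (emergency department triage): "Depending on available resources, context specific forms might include multimodal computerized tomography (CT) including noncontrast CT, CT angiography, and CT perfusion", for code stroke patients with suspected LVO.
- Table 2 lists "Combined CT/CTA on code stroke patients with suspected LVO" in the column of optional or tailored strategies, not among the required core functions.
- Ethics and Dissemination: evaluation is standard care, as clinically indicated.

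No section requires vessel imaging in patients with EMSA below 4, and none says how a patient without it is coded or analysed.

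**The concern.** The inference from the recorded fields to the two accuracy measures has a gap. A confirmed LVO is evidence of presence. The lack of a confirmed LVO covers two different patients: one imaged and found clear, and one never imaged. True and false negatives can be told apart only in the first group.

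The gap would do little harm if imaging were unrelated to the screen, but the article points the other way. Hospitals receive item-level EMSA results in the prenotification, and the imaging strategies are aimed at suspected LVO. During TCC Coordinated SBST, screen-positives are also routed to thrombectomy centers where limits allow, or are followed up every 20 minutes at other centers, and local imaging protocols may change. Verification could then differ by screen result and by phase, and apparent accuracy could move with no change in the screen itself.

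At stake is the count of patients whom the triage misses. The Discussion itself names false negatives as a known weakness of severity scales. The Table 3 outcome on thrombectomy among all confirmed stroke-system LVO depends on the same verification.

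**Working it through.** **Inputs from the protocol article (Sample Size Estimates), per year**

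- 7,630 stroke-system patients; 10%, 5% and 10% removed: 7,630 × 0.75 = 5,722.5 (stated 5,722).
- EMSA ≥ 4 in 41%: 5,722 × 0.41 = 2,346.0 (stated 2,346).
- LVO in 18% of these: 2,346 × 0.18 = 422.3 (stated 423).

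The plan's counts reproduce. Screen-negatives are 5,722 − 2,346 = 3,376. I take 423 as the true positives (TP), so false positives are 2,346 − 423 = 1,923.

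**Assumptions (not in the documents)**

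- LVO prevalence *p* in screen-negatives: 1%, 3% or 5%. False negatives FN = 3,376 × *p* = 33.8, 101.3 or 168.8.
- Share imaged: v₊ in screen-positives, v₋ in screen-negatives, unrelated to LVO status once the screen result is known.

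**Sensitivity**

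True: TP / (TP + FN). Observed: TP·v₊ / (TP·v₊ + FN·v₋).

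The observed formula is the same whether un-imaged patients are coded LVO-negative or left out, because in both cases only imaged LVOs enter it. Example at *p* = 5%, v₊ = 0.9, v₋ = 0.3: 380.7 / (380.7 + 50.6) = 88.3%, against a true 423 / 591.8 = 71.5%.

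| Sensitivity | p = 1% | p = 3% | p = 5% |
|---|---|---|---|
| True | 92.6% | 80.7% | 71.5% |
| v₊ 0.9, v₋ 0.6 | 94.9% | 86.2% | 79.0% |
| v₊ 0.9, v₋ 0.3 | 97.4% | 92.6% | 88.3% |
| v₊ 0.6, v₋ 0.6 | 92.6% | 80.7% | 71.5% |
| v₊ 0.3, v₋ 0.6 | 86.2% | 67.6% | 55.6% |

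With 90% against 30–60% imaging, the overstatement runs from 94.9 − 92.6 = 2.3 points to 88.3 − 71.5 = 16.8 points. Equal imaging gives no bias. The last row reverses it.

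**Specificity at p = 3%**

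- True: (3,376 − 101.3) / (3,376 − 101.3 + 1,923) = 63.0%.
- Un-imaged coded negative, v₊ 0.9: 62.8% (v₋ 0.6) or 63.0% (v₋ 0.3), so almost unchanged.
- Un-imaged excluded, v₊ 0.9: 53.2% (v₋ 0.6) or 36.2% (v₋ 0.3).

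**Shift between phases**

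If rollout raised imaging in screen-positives from 60% to 90% while screen-negatives stayed at 30%, observed sensitivity at *p* = 3% would go from 89.3% to 92.6%, with the screen unchanged.

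**The case against.** The strongest reply is that the article does not show the fault occurring.

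- **Forms.** The listed fields are introduced as examples, and the data collection forms are in a supplement not shown here. They may already separate imaged from un-imaged patients. This stands, and it makes the new field conditional.
- **Coding.** A reader might infer that un-imaged patients will be counted as LVO-negative and that this causes the inflation. No section says so, and the coding is not the driver: exclusion gives the same sensitivity. The cause would be less imaging in screen-negatives.
- **Who is imaged.** Table 2 also lists EMSA, another LVO scale or NIHSS on arrival, so suspicion in the emergency department can lead to imaging after a negative prehospital screen. Nothing limits CT angiography to prehospital EMSA ≥ 4. This stands. If such reassessment picks out true LVOs, the share of missed LVOs that get verified exceeds the overall imaging share, and the bias is smaller than tabulated.
- **Phase.** Rerouting applies only to screen-positives, and no section says that thrombectomy centers image more. If screen-positive verification is already high, the shift is small: raising it from 95% to 100% (*p* = 5%, v₋ = 60%) moves observed sensitivity from 79.9% to 80.7%. A larger shift needs lower baseline imaging or changed emergency department practice.
- **Missing-data plan.** Statistical Analysis provides for a missingness indicator, multiple imputation and sensitivity analyses. That helps only if imaging status is recorded, so that an un-imaged patient can be recognised as missing the reference standard.
- **Importance.** These measures appear in one narrative sentence. They are not the primary outcome and are not in Table 3. A reader might also infer that the accuracy results will set routing thresholds elsewhere. The article says only that it hopes the process will carry over to other contexts.

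**Conclusion.** The unqualified statement that sensitivity and specificity can be determined is not supported by the fields on which it rests. Vessel imaging is not required in screen-negatives, and the article's own description makes verification that depends on the screen result likely, though not certain.

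The direction is conditional. Sensitivity is overstated if screen-negatives are imaged less, under either simple handling of un-imaged patients. Specificity is seriously distorted only if they are excluded and imaging differs between the screen groups. The figure of about 2 to 17 points for sensitivity rests on assumed prevalence and imaging rates, on 423 being the full LVO count in screen-positives, and on imaging being unrelated to LVO within each screen group. It illustrates the scale and is not an estimate for this trial.

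The point is worth acting on but secondary. It does not touch the definition or power of the primary outcome.

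**What to change.** 1. Unless the forms already do so, record for every stroke-system patient, whatever the EMSA score, whether vessel imaging was done (yes/no). This needs no change to who is imaged.
2. Report the share imaged by screen result, hospital level and phase.
3. Estimate sensitivity and specificity with a verification-bias correction (inverse-probability weighting or Begg–Greenes), conditioning on EMSA score, hospital level, phase and any recorded arrival severity. The REDCap hospital data are described for study patients, so arrival severity may be lacking in screen-negatives; the correction should not be presented as complete.
4. Give bounds by phase, with un-imaged patients set first to all LVO-negative and then to a plausible LVO rate.
5. Reword the sentence in Secondary Outcomes to say that accuracy will be estimated subject to incomplete verification by vessel imaging.

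The cost is at most one extra field on data that coordinators already abstract, and a modest added analysis. The article reports that patient enrollment was still pending, so the field is cheaper to add at the start than to recover later.

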### Mixed Methods Multi-Phase Design

A recent prehospital stroke system of care consensus conference advised collaboration of regional stakeholders to create an optimally adapted prehospital stroke system (23). A mixed methods methodological approach which aims to integrate rigorous quantitative and qualitative methods within a study will be the most effective way to understand varied and multi-level stakeholder perceptions and optimize implementation of this complex health intervention across different service contexts (24). We will use a multi-phase QUAL+QUAN → QUAN → QUAL mixed methods design to assess stakeholders' views about the implementation process capitalizing on the advantages of integrating quantitative and qualitative methods using surveys and quantitative measures, focus groups and individual semi-structured interviews (24–27). We will use quantitative and qualitative methods to aid in the development of context specific forms of the model prior to implementation (28–30). Quantitative data will include patient-specific factors (EMSA score, Alert, responds to Voice, responds to Pain and Unresponsive scale, time last known well, potential tPA eligibility, vital signs), EMS factors (EMS air and ground resources, estimated travel times to nearest available non-MTC and MTC), and hospital factors (stroke center level, imaging, and treatment capabilities, location). Qualitative data consisting of focus groups and interviews with stakeholders will be critical for development of regional triage plans and stroke center protocols. An example Focus Group Guide for the TCC paramedic communicators is available (Supplementary Material 1). After implementation, we will survey stakeholders to assess perceptions of feasibility, appropriateness, and acceptability of the intervention and employ follow-up qualitative interviews with purposefully selected individuals to understand context-specific barriers and facilitators more fully to intervention adoption, implementation, maintenance, and spread. Systematic integration and triangulation of quantitative and qualitative data will assure more valid conclusions (31).

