**Figure 3 F3:**
[figure not shown]
Flow of patients during study. The study will include prehospital patients entered into the stroke system by EMS with an EMSA ≥ 4. Patients with a time last known well (LKW) > 24 h or those who respond only to pain or who are unresponsive will be excluded. During the standard triage period, patients meeting study entry criteria will be transported to the closest stroke center with capacity. During TCC Coordinated SBST, patients will be routed by TCC directly to a MTC (including comprehensive stroke centers and thrombectomy-capable primary stroke centers) if additional transport time complies with region-specific transport time limits and will not preclude use of tPA. Otherwise, TCC will coordinate transport to the closest stroke center of any level and initiate a region and hospital specific plan to expedite inter-facility transfer to a MTC for appropriate patients.

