	• Differential effectiveness by race, ethnicity, sex, and population density	• LifeTrac and ADPH REDCap databases
	• Differential effectiveness for patients initially triaged to a non-MTC	• LifeTrac and ADPH REDCap databases
	• modified Rankin Scale 3 months after discharge	• ADPH REDCap databases
	• County/Regional EMS response times	• ADPH RESCUE ePCR
**Adoption**	• Proportion of Alabama EMS organizations that participate	• ADPH RESCUE ePCR and LifeTrac database
	• Proportion of stroke centers participating	• ADPH RESCUE ePCR
**Implementation**	• Proportion of stroke system patients with TCC-guided EMSA performed by EMS	• LifeTrac database
	• Proportion of EMS transports triaged past a non-MTC to a MTC when advised	• LifeTrac database
	• TCC and stroke center adherence to the region-specific triage plan	• LifeTrac and ADPH REDCap databases
	• Differential implementation for rural vs. urban populations	• LifeTrac and ADPH REDCap databases
**Maintenance**	• Sustained adoption and implementation over time	• LifeTrac and ADPH REDCap databases

*RE-AIM, Reach, Effectiveness, Adoption, Implementation, and Maintenance; TCC, Trauma Communications Center; SBST, Severity-Based Stroke Triage; ADPH, Alabama Department of Public Health; RESCUE ePCR, Recording of Emergency Medical Services Calls and Urgent-care Environment electronic Patient Care Reports; LVO, Large Vessel Occlusion; MT, Mechanical Thrombectomy; EMS, Emergency Medical Service; tPA, tissue Plasminogen Activator; MTC, Mechanical Thrombectomy Center*.

After implementation, we will use validated, quantitative surveys of stakeholders to assess perceptions of feasibility, appropriateness, and acceptability of the intervention (40). We will employ follow-up qualitative interviews with purposefully selected individuals to identify barriers and facilitators to adoption, implementation, maintenance, and spread using a mixed methods approach (AIM 3). This will help identify context-specific strategies to guide implementation efforts elsewhere.

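### Effectiveness in patients first taken to a non-MTC, and timeliness of transfer, are compared before and after in a group whose make-up the intervention itself changes

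*Protocol article*

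**What the plan says.** All references are to the protocol article.

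- **Contrast.** The Secondary Outcomes section introduces the RE-AIM outcomes of Table 3 with "we seek to fully assess change in the broad public health impact before and after implementation of TCC Coordinated SBST".
- **Outcomes at issue.** Under Effectiveness, Table 3 lists "Differential effectiveness for patients initially triaged to a non-MTC" and "Proportion requiring inter-facility transfer and timeliness of transfer".
- **Routing before implementation** (Figure 3 legend): "During the standard triage period, patients meeting study entry criteria will be transported to the closest stroke center with capacity".
- **Routing after implementation** (Figure 3 legend): patients go directly to an MTC "if additional transport time complies with region-specific transport time limits and will not preclude use of tPA". For the rest: "Otherwise, TCC will coordinate transport to the closest stroke center of any level and initiate a region and hospital specific plan". The Intervention section, item 3, gives the same condition from the other side: "If direct transport time to a MTC is greater than region-specific limits or transport to a MTC will preclude use of tPA".
- **Models.** Statistical Analysis of Stepped Wedge Data names mixed models, GEE and Cox regression for secondary endpoints. It does not define the non-MTC group by anything other than where the patient was taken.
- **Data.** Mixed Methods Multi-Phase Design lists time last known well, potential tPA eligibility and "estimated travel times to nearest available non-MTC and MTC" among the quantitative data.

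**The concern.** The subgroup is defined by actual first destination, which is the first thing the intervention acts on. Patients who can be redirected to an MTC leave the group when their region crosses over. Those who stay tend to be farther from an MTC or to have a tighter tPA window. A before-after difference in thrombectomy rate or in transfer time then mixes two things: any real improvement in emergency department and inter-facility care, and the change in who is left.

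The stakes are real although the outcome is secondary. Aim 1 includes coordinating inter-facility care, and the Discussion calls continued coordination for patients first taken to a non-MTC an important aspect of the protocol. Under Interim Analysis, secondary endpoints after implementation in Regions 3 and 5 are to guide training and delivery in Regions 1, 2, 4 and 6. The article names two in-state MTCs in each of Regions 3 and 5 and none in Regions 2 and 4. The shift in case mix may therefore differ between the regions that produce the interim signal and those that act on it.

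**Working it through.** **1. Who is in the non-MTC group in each phase**

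| Patient whose closest available center is a non-MTC | Standard triage | SBST |
|---|---|---|
| Within the regional limit, direct transport does not preclude tPA | in the group | leaves it, unless not bypassed as advised |
| Beyond the regional limit | in the group | stays |
| Direct transport would preclude tPA | in the group | stays |

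The after group is roughly a subset of the before group. Table 3 itself counts transports taken past a non-MTC when advised, so the plan expects the first row to move.

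**2. Whether the stated models would remove the shift.** A region term absorbs stable differences between regions. A calendar-time term absorbs changes common to all regions. This shift occurs inside each region at its own crossover, so it coincides with the intervention indicator and is attributed to it.

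**3. Reading the line as an interaction** (non-MTC versus direct to MTC) does not help. The redirected patients move from one side of the contrast to the other, so both sides change.

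**4. What the shift can do.** The plan gives no figure for this outcome. The nearest is the statewide thrombectomy rate in suspected LVO from Sample Size Estimates: 211/2,346 = 9.0%. It includes patients whose closest center is an MTC, so it serves only as a rough anchor. Everything else here is assumed.

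Let s be the share of the before group that SBST redirects, a the rate in those patients, and b the rate in those who stay. With no true effect in either stratum:

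before = s·a + (1 - s)·b; after = b; false change = s·(b - a).

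| s | a | b | before | after | relative change |
|---|---|---|---|---|---|
| 0.5 | 11% | 7% | 9.0% | 7.0% | -2.0/9.0 = -22% |
| 0.3 | 10% | 8% | 8.6% | 8.0% | -0.6/8.6 = -7% |
| 0.7 | 12% | 6% | 10.2% | 6.0% | -4.2/10.2 = -41% |
| 0.3 | 8% | 10% | 9.4% | 10.0% | +0.6/9.4 = +6% |
| 0.7 | 8% | 10% | 8.6% | 10.0% | +1.4/8.6 = +16% |

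If a = b the false change is zero.

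**5. Hiding a true effect.** On the scale of confirmed LVO, where the plan uses a reference of 50%, assume a = 55% and b = 35%, with a true gain of 10 points in those who stay (35% to 45%). Apparent change = 45 - (s·55 + (1 - s)·35):

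- s = 0.25: 45 - 40 = +5 points
- s = 0.50: 45 - 45 = 0
- s = 0.75: 45 - 50 = -5 points

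**6. Transfer time.** Assume 90 min in redirectable patients and 120 to 150 min in the others, with care unchanged. The smallest case in this range is s = 0.25 with 120 min: before = 0.25·90 + 0.75·120 = 112.5, after = 120, so +7.5 min. The largest is s = 0.75 with 150 min: before = 0.75·90 + 0.25·150 = 105, after = 150, so +45 min.

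**7. Proportion transferred.** If the denominator is all LVO patients, as the Secondary Outcomes text suggests, it does not condition on destination and is not affected.

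**The case against.** The strongest reply is that one line of a table in a condensed article is not a full analysis specification. Adjustment for case mix may sit in an analysis plan that is not shown. That is fair for covariates and model detail. It does not rescue the definition: the article fixes the group by where patients were first taken and assesses Table 3 before and after.

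A reader might infer more than the documents support, and these limits stand:

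- **Two separate kinds of patient.** No: the mix changes, but the after group is roughly contained in the before group.
- **Only remote patients remain.** No: patients limited by the tPA condition also stay, wherever they are, as do any not bypassed as advised.
- **No other outcome addresses the inter-facility arm.** No: transfer timeliness and stroke center adherence to the triage plan also bear on it. Differential effectiveness by population density gives a partial view that triage does not determine.
- **The pathway will look harmful.** Not shown: the shares, stratum rates and minutes have no source in the document, and the sign depends on them.
- **Every transfer measure is distorted by distance.** The article does not define the interval. Door-in door-out time, which the Discussion mentions, excludes travel to the MTC and would be less sensitive to distance, though its patient and hospital mix would still change.

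It is also true that the travel times are listed as data for developing regional plans. The article does not say that they are recorded for each standard-phase patient.

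**Conclusion.** The point holds as a flaw in how a secondary-outcome subgroup is fixed. It follows from the routing rules and the before-after contrast and does not depend on the illustrative numbers. Timeliness of transfer is affected for the same reason.

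The size is unknown. Zero true effect appears as anything from -41% to +16% in relative terms under the first set of assumptions, and as +7.5 to +45 min for transfer time under the second. These ranges show what a changed mix can do, not what it will do in Alabama.

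One might be tempted to extend the criticism to the trial's main result, but the documents do not support that. The primary outcome, and thrombectomy among all EMS-suspected or all confirmed LVO, do not condition on destination. The change should be made, but it does not threaten the primary analysis.

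**What to change.** - Keep the result by actual first destination as descriptive only.
- For the before-after comparison, define the group identically in both phases from facts that precede triage: scene location, estimated travel times to the nearest non-MTC and MTC, and time last known well. The group is the patients whom the region's own final SBST rule, as adopted, would send to a non-MTC. Report the complementary group (would go directly to an MTC) alongside.
- Derive this variable by the same method in both phases. Using live routing data in the SBST phase and reconstruction in the standard phase would misclassify patients differently before and after.
- For timeliness, report time from first EMS contact to MTC arrival or to thrombectomy within these groups, together with the proportion who reach that point.

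With this definition the routing-induced change in composition is removed by construction, apart from misclassification. No clinical rule is altered.

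**Cost.** Revised analysis wording and a derived variable for each patient. Travel times may have to be computed from scene location, and it should be confirmed that the inputs are captured during standard triage. Some misclassification will remain, because weather, air availability and resources also affect real routing. The Study Timeline section says patient enrollment is pending, so the definition can still be set before data accrue.
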